### Exclusion criteria

Subjects presenting any of the following exclusion criteria will not be included in the trial:

1. currently using other NRT, bupropion, nortriptyline, mecamylamine, reserpine, or varenicline, or undergoing any treatment for tobacco dependence (e.g. acupuncture),

2. unstable angina pectoris, myocardial infarction, or cerebrovascular accident during the last 3 weeks,

3. severe cardiac arrhythmia

4. currently uncontrolled hyperthyroidism

5. active phaeocromocytoma

6. pregnancy, lactation or intended pregnancy

7. suspected alcohol or drug abuse

8. participation in other medicinal trials within the last three months and during study participation,

9. previously had severe skin reactions to nicotine patches or severe eczema or other skin diseases that make patch use hazardous or undesirable.

10. a severe acute or chronic medical or psychiatric condition or previously diagnosed clinically important renal or hepatic disease, that may increase the risk associated with study participation or may interfere with the interpretation of study results and, in the judgment of the investigator, would make the subject inappropriate for entry into this study.

### Withdrawal criteria

Trial Withdrawal: It is standard practice in smoking cessation trials to regard those who fail to attend for support and treatment as having relapsed, which is based on some evidence[20]. Therefore, failure to attend will not count as withdrawal from the trial and the only withdrawals will be those where a patient asks to be withdrawn. Such patients will not be replaced and, unless s/he refuses permission, data available up to that point will be used. Such withdrawals are expected in fewer than 5% of participants. This is standard procedure in smoking cessation studies.

Treatment withdrawal: One of our exclusion criteria is previous adverse reactions to NRT; so given that most smokers have used NRT recently, the established safety profile of NRT and the evidence from trials of combination NRT, we do not expect any serious adverse events due to the medication. Nevertheless, there will be a detailed work instruction for the trial that will detail the weekly assessment of side-effects, and the procedure for serious adverse events (SAE) and suspected unexpected serious adverse reactions (SUSARs). In the event of an SAE or SUSAR that is judged either possibly, probably, or definitely related to NRT, the prescription for NRT will be withdrawn and not re-instituted in that person.

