In this study, we propose using both nicotine patch and an acute form of NRT in combination (See Table 1). We will use Niquitin, Nicotinell, Wockhardt, and Nicorette NRT products, including 24 hour patches, which are licensed for 16 hour use also (there is no evidence that the effectiveness of 16 hour patches or 24 hour patches is different[33]). These patches provide about 1 milligram (mg) per hour of nicotine. Participants will be advised to wear the patch 24 hours per day, but will be advised to wear it only during day time should they experience sleep disturbance or vivid dreams. Although the medications provide the same amount of nicotine delivery with similar pharmacokinetics, the license dosing advice differs. Niquitin CQ recommend the 21 mg patch for smokers who smoke 10 or more cigarettes per day, while Nicotinell recommend the 30 cm^2 ^(= 21 mg) patch for smokers of 20 or more cigarettes per day. The evidence is that most smokers who smoke 10 or more cigarettes per day get less nicotine from their patch than they did from their cigarettes[34,35]. We have therefore chosen a cut-off of 15 cigarettes per day. In addition, all participants will be offered additional intra-nasal or oral nicotine replacement (gum, microtabs, lozenges, or inhalator) with the choice of delivery system left to personal preference. The dose of these products used will vary, but participants will be advised to take at least 1 mg of absorbed nicotine for each cigarette forgone in the reduction phase because each cigarette delivers about 1.2 mg on average, though this is highly variable[36]. A 2 mg oral product, for example gum, delivers about 1 mg available systemically, and a 10 mg inhalator cartridge yields about 3 mg of nicotine that is systemically available. In the cessation phase, participants in both arms will be given identical dosing instructions and advised to use at least 6 mg of absorbed nicotine daily, which is the minimum dose associated with improved outcomes[33].

**Table 1 T1:** Daily medication regimes

	**Rapid reduction**	**Abrupt cessation**
**Pre-quit period -2 weeks to quit day**	21 mg/24 hour patch, 1 mg of absorbed nicotine per cigarette forgone as a minimum from acute NRT.	21 mg/24 hour patch, No acute NRT.

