### Evidence of safety of smoking whilst using NRT

The safety of using transdermal NRT while smoking was investigated in a review by Fagerstrom & Hughes[37], which is summarised in Table 2. In addition to this review, we have recently systematically reviewed the Cut Down to Stop (CDTS) studies mentioned in the literature review[19]. As part of this, we performed a meta-analysis of adverse events in people smoking and using NRT versus those smoking and using placebo NRT. Overall, 1384 predominantly middle-aged smokers were treated with NRT for 6 to 18 months, while 1383 were treated with placebo. Four deaths occurred in those randomised to NRT and four in those randomised to placebo; Odds ratio (OR) 1.00 95%CI 0.25–4.02. Serious adverse events occurred in fewer than 8% of participants in both arms; OR 1.09 95%CI 0.79–1.50. In no cases were these were judged likely to have been due to treatment. Discontinuation of treatment due to adverse events was rare with 1.7% and 1.3% in the NRT and placebo groups; OR 1.27 95%CI 0.64–2.51. Nausea was selected as an index symptom to indicate possible nicotine overdose. It was slightly and significantly more common in the NRT group with 8.6% versus 5.3% on placebo experiencing nausea; OR 1.69 95%CI 1.21–2.36.

**Table 2 T2:** Summary of Fagerstrom & Hughes review of the safety of smoking and concomitant NRT use[37]

**Study reviewed**	**NRT treatment given**	**Blood nicotine concentrations**	**Safety conclusions**
Foulds et al, 1992	16+ cigarettes per day (cpd) & 15 milligram (mg) transdermal patch (TP) over 16 hrs	Baseline: 37 nanograms per millilitre (ng/ml), Placebo: 36 ng/ml, 15 mg TP: 44 ng/ml.	Participants experienced almost no subjective toxic effects whilst wearing the patch

Pickworth, Bunker & Henningfield, 1994	13+ cpd & 22 mg, 44 mg TP over 24 hrs	Baseline: 30 ng/ml, Placebo: 19 ng/ml, 22 mg TP: 39 ng/ml, 44 mg TP: 63 ng/ml.	No adverse subjective experiences were reported.

Mahmarian et al, 1997	8+ cpd & 14 mg TP over 24 hrs	Baseline 16 ng/ml, 14 mg TP: 24 ng/ml, 21 mg TP: 30 ng/ml.	Only adverse effects noted were nausea & vomiting in 2 patients.

Zevin, Jacob & Benowitz, 1998	Smoking ad libitum & 21 mg, 42 mg, 63 mg patch over 8 hours	Placebo: 20 ng/ml, 63 mg TP: 60 ng/ml.	No additional haemodynamic effects of TP on heart rate, blood pressure, noradrenaline, white blood cell count, fibrinogen, haematocrit, cortisol, or lipids. No adverse reactions.

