### Safety Reporting

#### Assessment of safety

Potential participants' safety will be ensured by screening for eligibility using a structured form completed by the trial nurse. This will record evidence of eligibility and exclusion criteria. In addition, the nurse will take a general medical history to assess for other complicating diseases. Any queries remaining as a result of this process will be resolved by discussion between the trial nurse, chief investigator and the relevant physicians providing routine medical care, usually the participant's general practitioner. Such concerns are unusual but not rare. Typically, they arise from a participant's hazy knowledge or understanding of their past medical history and are usually readily resolved. No blood or further medical testing will be necessary to ensure safety.

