NRT has been investigated in several hundred previous clinical trials and is widely prescribed worldwide and subject to safety monitoring, and is replacing a product, nicotine, which the participants are already consuming and will have consumed for many years in cigarettes. Thus, there is every reason to expect that treatment in this trial will be safe. Participants will be warned about the side-effects of NRT and advised not to stop taking the medication without consulting with an NHS professional, preferably the trial team. To this end, all participants will be given a credit card-sized card with the trial team's contact details on that will allow participants to receive advice on medication or to report perceived serious adverse effects and receive advice on medication as required. Participants will record the occurrence of side-effects of medication as specified on the summary of product characteristics for relevant NRT preparations, by completing a checklist. The checklist will be given to the trial nurse and the nurse will enquire about recorded adverse events, so as to determine the severity of any adverse event and ensure that appropriate advice is given for its management (such as rotating the patch site or use of emollients for skin reactions). Minor adverse reactions will be monitored and managed in this way. For each known side effect listed in the summary of product characteristics, the trial nurse will have a definition of clinical severity. For example, a mild skin site reaction to the patch will be defined as burning sensation that does not interfere with normal activities, redness or swelling at the site of application, or mild blistering. Any reaction beyond that will be classified as potentially moderate or severe and will be reported to and discussed with the principal investigator. A decision on stopping therapy will then be made with the participant, attending clinician, principal investigator, and other relevant parties as appropriate. Nicotine has a short half life (2 hours), meaning that the blood concentration will not build up during the course of treatment so that new side-effects are not expected after the first few weeks. In addition, with reactions relating to local use, such as skin discomfort from patches, or bad taste from oral use, either treatment will have been switched or people become accustomed to the side-effects after a short time of using the preparation. At the last meeting (week 8 of the quit attempt), the participant will be advised to phone the contact number to report side-effects that occur after this. The advice given will depend upon the severity of the reported reaction and those with moderate reactions will be invited to an ad hoc consultation.

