
Participants will also complete a schedule of nicotine overdose symptoms at each visit. On completion of this questionnaire, the schedule will be handed to the nurse and thus any symptoms of overdose will be assessed. In addition, based on her/his enquiry, the nurse will make an assessment of whether the NRT dose is too high or not, and then what action was taken, such as continue with prescribed dose, or direct the participant to use a lower dose, which will be recorded.

The summary of product characteristics for the relevant NRT products contain no warnings about serious adverse reactions except rare allergic reactions, such as angioedema, and cardiac arrhythmias, occurring in less than 1/1000 users. Thus we expect no or very few suspected unexpected serious adverse reactions (SUSARs) in this trial. The long history of use in and outside of trials for NRT means that SUSARs are unlikely. On the reverse of the trial card given the contact number for advice on side-effect management, there will be instructions for the reporting of serious adverse events. Through direct contact from the participant or contact from their attending physician, we expect to become aware of serious adverse events. If any member of the trial team becomes aware, they will inform the PI within 24 hours. The principal investigator will then assess the seriousness, causality, expectedness and severity of the adverse effects. An immediate decision will be made on the interim use of medication for that participant. If an event is judged severe, it will be reported to the trial sponsor, who will report the event to the Research Ethics Committee and Medicines and Healthcare Regulatory Authority. Participants will be asked weekly to report inter-current illnesses and the response recorded. If any of these inter-current illnesses contra-indicates NRT, this will be immediately reported to the principal investigator and a decision made about continued use of the NRT product. The reporting procedures and definitions are presented in Additional file 1.

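### The Withdrawal criteria section relies on an exclusion for past reactions to NRT, but the exclusion list covers only severe skin reactions to patches

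*Protocol article*

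**What the plan says.** The Withdrawal criteria section, under treatment withdrawal, says: "One of our exclusion criteria is previous adverse reactions to NRT". It combines this with most smokers' recent use of NRT, the drug's established safety record and the combination-NRT trials, and concludes that no medication-related serious adverse events are expected. It also says that if a serious event judged at least possibly related to NRT does occur, NRT is withdrawn and not given to that person again.

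The Exclusion criteria section lists ten numbered items. The only one about a past reaction to NRT is item 9: "previously had severe skin reactions to nicotine patches or severe eczema or other skin diseases that make patch use hazardous or undesirable".

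Under Trial Medication, patches are not the only product: "all participants will be offered additional intra-nasal or oral nicotine replacement". Under Assessment of safety, the NRT product summaries are said to "contain no warnings about serious adverse reactions except rare allergic reactions, such as angioedema, and cardiac arrhythmias, occurring in less than 1/1000 users". The same section describes the structured eligibility form that the trial nurse completes: "This will record evidence of eligibility and exclusion criteria".

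**The concern.** The sentence in Withdrawal criteria describes an exclusion that the list does not contain. It covers any NRT product and any kind of reaction. Item 9 covers one product form and one organ, and only when severe.

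Recent NRT use among volunteers reassures about serious events only if those who reacted badly have been screened out. As listed, only people with severe skin reactions to patches are. Someone with past angioedema on gum, for example, could be entered and offered the same class of product without meeting a listed exclusion on that account. Within the trial, the same event would end NRT for that person permanently. Past and in-trial reactions are thus handled differently for no stated reason.

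What is at stake is the soundness of the safety rationale and the clarity of screening. The efficacy comparison is not in question.

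**Working it through.** The plan gives no figure for this point, so the main check is a comparison of text. A short calculation then gives the size.

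**Step 1: could any listed item cover a past serious reaction to NRT?**

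- Item 1 concerns current use of NRT or other cessation treatment, not past reactions.
- Item 3 excludes severe cardiac arrhythmia whatever its cause. It covers part of the arrhythmia risk and no allergic reaction.
- Item 9 covers severe skin reactions to patches and skin disease. It leaves out non-skin reactions to patches and all reactions to gum, microtabs, lozenges, inhalator or nasal NRT.
- Item 10 is a matter of investigator judgement about severe medical or psychiatric conditions and renal or hepatic disease. It does not name drug reactions, and a resolved allergic reaction is not obviously a condition of that kind.
- Items 2 and 4 to 8 concern other matters.

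No item lists a past serious non-skin reaction to NRT, or a past serious reaction to an oral or nasal product.

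**Step 2: does the gap matter for the products used?** Oral or nasal NRT is offered to everyone. Under Stopping rules/modification of medication regime, patch users with uncontrolled skin reactions move to acute NRT alone. The protocol itself names angioedema among the labelled serious reactions. The unlisted reactions are therefore relevant to the trial treatment.

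**Step 3: how many people?**

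- Rate of labelled serious reactions: under 1/1000 users (Assessment of safety), taken as allergic reactions and arrhythmias combined.
- Enrolment: 700 (Power calculation).
- Share with past NRT use: assumed 50–100%. The protocol says only that most smokers have used it recently.

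Expected number < 700 × share × 0.001

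- At 50%: 700 × 0.5 × 0.001 = 0.35
- At 100%: 700 × 1.0 × 0.001 = 0.70

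The text does not say whether 1/1000 is a combined rate or applies to each reaction. If it applies to each, allergic reactions alone still give at most 0.35–0.70. Arrhythmias would add up to the same again, but item 3 already removes severe arrhythmia. The bound makes no deduction for what the medical history would catch, or for people with a past serious reaction choosing not to volunteer.

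**The case against.** The strongest reply is that the sentence in Withdrawal criteria is a loose paraphrase of item 9, that the numbered list is the operative one, and that little is left uncovered. The nurse takes a general medical history, and "Any queries remaining as a result of this process will be resolved by discussion between the trial nurse, chief investigator and the relevant physicians". Participants choose their own acute product, so someone who reacted to one can avoid it. The safety expectation also has other grounds, and procedures exist for serious events if they arise. All of this is fair, and it is why the point is minor. None of it is a listed criterion, however, and even as a paraphrase the sentence is wrong. Condensation for a journal does not explain it either: the article prints a numbered list and then misdescribes it.

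Narrowing the sentence to match item 9 would also remove the contradiction. It would leave the screening gap, and it would still treat a past serious reaction more leniently than one during the trial.

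A reader might infer something stronger: that the two sections set up competing eligible populations, and that many volunteers with mild past effects would be turned away. Nausea is common enough to suggest this; the review of smoking with concurrent NRT reports it "with 8.6% versus 5.3% on placebo experiencing nausea". The documents do not support that reading. The screening form records the listed criteria, so nobody is refused because of a passing sentence in another section. The nausea rate also comes from 6 to 18 months of NRT use while smoking, not from volunteers' past courses.

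**Conclusion.** The inconsistency is real and lies within the current text. The protocol bases part of its safety expectation on an exclusion that its list does not contain, and past serious reactions to NRT other than severe skin reactions to patches are not a listed ground for exclusion. It should be corrected as a minor safety and consistency matter. Fewer than one person per 700 is expected to be affected (upper bound 0.35–0.7), assuming 50–100% past NRT use and the protocol's own combined rate for labelled serious reactions. Sample size, power and the primary result are unaffected. The documents do not show that participants face a material safety risk or that safety monitoring is inadequate.

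**What to change.** Make three small edits.

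1. Add to Exclusion criteria: *11. previous serious reaction (for example angioedema) to any nicotine replacement product.*
2. Add the matching yes/no question to the structured eligibility form described under Assessment of safety.
3. Replace the first clause of the sentence in Withdrawal criteria with: *Our exclusion criteria include previous severe skin reactions to nicotine patches (item 9) and previous serious reactions to any NRT product (item 11).*

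Keep the new item to serious reactions. An unqualified reference to hypersensitivity, or to any adverse reaction, could exclude people with mild patch reactions whom item 9 leaves eligible. The trial already manages such reactions by switching preparation, emollients or hydrocortisone cream; Assessment of safety says: "Minor adverse reactions will be monitored and managed in this way". Mild or local reactions and past nausea should not exclude anyone.

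The cost is one line, one question and one reworded clause. Fewer than one extra exclusion per 700 is expected. It would occur before randomisation, so the planned 700 and the power stand.

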### Participant Recruitment

We will recruit participants through South Birmingham, Solihull, Heart of Birmingham and Warwickshire and Worcestershire Primary Care Trusts in several ways. We will request that general practitioner's practices write to patients on their practice lists recorded as smokers and offer them treatment. We will also request that the stop smoking services write to people on their databases who have tried to stop and failed. The letters sent out will ask those patients who wish to take part in the trial to respond to the research team. In our experience, 5–10% will respond. Finally the trial treatment will also be offered to people booking for treatment with stop smoking services. Following telephone screening for preliminary eligibility, potential participants will be booked in for an assessment visit. Written informed consent will be obtained from participants at the first assessment session before they have been randomised to a treatment arm.

Participants in both treatment arms will be seen weekly for 2 weeks prior to quit day, on quit day, and weekly for 4 weeks post-quit. A further follow-up visit will take place 8 weeks post quit-day and a final follow-up phone call at 6 months. Therefore all participants will be enrolled in the trial for 6 months and 2 weeks.

It is not unusual for people to delay their quit day, once committed, for a variety of reasons, e.g. death of a close family member or friend. In this situation we will allow participants to delay their quit attempt for a maximum of 2 weeks. They will be advised to carry on with their pre quit NRT regime as prescribed and their actual quit date appointment will be recorded as their visit 3 appointment. Extra visits in between week 2 and week 3 will be recorded in the case record form and extra diaries and NRT will be issued to the participants to cover their delay period. Extra visit questionnaires will also be given to the participant for completion. Participants wishing to delay their quit day by >2 weeks will be classified as abandoning this quit attempt, NRT will be ceased and the participant will be advised to contact their local stop smoking service when they are ready to set a new quit date. They will be provided with the name and number of their local stop smoking service.

### Allocation to trial arms and treatments

#### Randomisation

Participants will be seen at an assessment session, similar to that used by stop smoking services, where participants will be randomised 1:1 to reduction or abrupt cessation in the assessment session. We will use Stata to accomplish stratified randomisation by therapist with blocking within each stratum to ensure balance. The blocks will be randomly ordered blocks of 2, 4, and 6. Each therapist will open sealed numbered envelopes in turn after consent and initial procedures to determine allocation to abrupt cessation or rapid reduction.

Participants in the reduction arm will be offered a choice of ways to reduce and asked to choose the method they feel is right for them. Those without strong preferences will be randomised to one of the three reduction methods. We will use Stata to accomplish stratified randomisation by therapist with blocking within each stratum to ensure balance. The blocks will be randomly ordered blocks of 3 and 6. Each therapist will open sealed numbered envelopes in turn after consent and initial procedures to determine allocation to abrupt cessation or rapid reduction.

It is quite likely that we will see couples, friends, or relatives who want to quit together and attend clinic as a group. In this situation they will be randomised together so they go into the same arm and given the same study number but made identifiable by adding an A or B to the end of their number.

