### Trial Statistics

#### Power calculation

We propose a non-inferiority trial following the Consolidated Standards of Reporting Trials (CONSORT) statement for such trials[29]. With a one-sided alpha of 0.05 we have 80% power to detect inferiority of 9.5% in the quit rate at four weeks if we enrol 343 in each arm, assuming 50% 4-week abstinence. Therefore the trial sample size shall be N = 700. Analyses will be carried out on an intention-to-treat basis, according to the Russell Standard, where participants lost to follow up are assumed to be smokers [20].

Arguably, differences of 5% at 4 weeks would be worthwhile detecting[50], but a trial would need to enrol 2500 participants for this, which would make it impractical and unlikely to be funded. If the reduction produced abstinence rates not worse than 9.5% less at four weeks, this is probably sufficient for stop smoking services to implement the programme.

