#### Analysis

The analysis will compare the proportions stopping smoking, calculating confidence intervals and relative risks and confidence intervals. We will calculate differences in withdrawal scores using regression, controlling for baseline differences, as is standard using the MPSS[51]. We will investigate possible mechanisms of action (NRT dose, satisfaction from smoking, withdrawal, self-efficacy) using mediation analysis within a regression framework. Mediation analysis is outlined in more detail by the RIPL research group at the Arizona State University[52].

In comparing methods of reduction, we have no specified hypotheses. We will compare changes in confidence, stereotypy, and urges to smoke calculating differences in mean changes and confidence intervals for the difference. We will compare the proportion abstinent using point prevalence and prolonged abstinence as in the comparison between reduction and abrupt cessation. The primary analysis of abrupt cessation versus reduction will not be adjusted by method of reduction used.

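### People who attend together are randomised as one unit, but the sample size assumes independent participants and the stated primary comparison makes no provision for the shared unit

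*Protocol article*

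**What the plan says.** **Allocation.** Under Randomisation, the protocol article allocates 1:1 and adds: "We will use Stata to accomplish stratified randomisation by therapist with blocking within each stratum to ensure balance". The same section anticipates that people who know each other will want to quit together, and rules: "In this situation they will be randomised together so they go into the same arm and given the same study number". A letter suffix (A or B) tells the members apart.

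**Sample size.** Under Power calculation: "With a one-sided alpha of 0.05 we have 80% power to detect inferiority of 9.5% in the quit rate at four weeks", and this holds "if we enrol 343 in each arm, assuming 50% 4-week abstinence". The total is then rounded up: "Therefore the trial sample size shall be N = 700". No allowance for joint allocation is mentioned.

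**Analysis.** Under Analysis: "The analysis will compare the proportions stopping smoking", with confidence intervals and relative risks. The section rules out adjusting the primary comparison for the method of reduction. It is silent on therapist, on other baseline covariates and on participants who share a study number.

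**The concern.** Two people placed in the same arm by one draw, who make their quit attempt together, are a cluster of two. If one member's abstinence makes the other's more likely, the pair carries less information than two unrelated people. A standard error that counts every participant as independent is then too small.

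The direction matters here. The trial concludes in favour of reduction if the lower confidence limit for the difference in four-week abstinence stays above minus 9.5 percentage points. An interval that is too narrow pulls that limit towards zero and makes non-inferiority easier to declare. At the same time, the power of an analysis that respects the pairs is below the figure planned.

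**Working it through.** **1. Inputs**
- From Power calculation: one-sided alpha 0.05, power 80%, margin 9.5 points, 50% abstinence assumed (taken in both arms), 343 per arm, N = 700 (350 per arm).
- Not in the article, so assumed: f, the share of participants in co-allocated pairs, and rho, the within-pair correlation of abstinence.

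**2. Reproducing the planned figure**

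n per arm = (1.645 + 0.842)² × [0.5 × 0.5 + 0.5 × 0.5] / 0.095² = 6.18 × 0.5 / 0.009025, which rounds up to 343.

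This matches exactly, with independent participants and no design effect. At 350 per arm the standard error is √(0.5/350) = 0.0378, and power = Φ(0.095/0.0378 − 1.645) = 80.7%.

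**3. Allowing for pairs**

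Each paired participant adds one covariance term of rho times the individual variance, so the design effect is DE = 1 + f × rho. Then:
- power of an analysis that respects the pairs = Φ(0.095/(0.0378 × √DE) − 1.645)
- true one-sided error of an interval that ignores them = Φ(−1.645/√DE)

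| f (assumed) | rho (assumed) | DE | n per arm for 80% power | Power at N = 700 | One-sided error, pairs ignored |
|---|---|---|---|---|---|
| 5% | 0.1 | 1.005 | 345 | 80.6% | 5.04% |
| 10% | 0.2 | 1.02 | 350 | 80.1% | 5.2% |
| 20% | 0.3 | 1.06 | 364 | 78.7% | 5.5% |
| 30% | 0.5 | 1.15 | 395 | 75.8% | 6.3% |
| 50% | 0.5 | 1.25 | 429 | 72.7% | 7.1% |

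Rounding up to 700 absorbs a design effect of 350/343 = 1.02, that is f × rho of about 0.02. Groups larger than two would raise DE further.

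**4. Therapist, which works the other way**

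Assume two equal therapist strata with 40% and 60% abstinence. The mean within-stratum variance is (0.24 + 0.24)/2 = 0.24, against 0.25 overall, a ratio of 0.96. Because allocation is balanced within therapist, an interval that ignores therapist is slightly too wide: the true one-sided error is Φ(−1.645/√0.96) = 4.7%. Including therapist lifts power from 80.7% to 82.1%.

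**5. Both together**

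If therapist is left out and both members of a pair see the same therapist, the true variance relative to the naive one is roughly [0.24 + f × (0.25 × rho − 0.01)]/0.25:
- f = 10%, rho = 0.2: 0.244/0.25 = 0.976, error about 4.8%
- f = 20%, rho = 0.3: 0.253/0.25 = 1.012, error about 5.1%
- f = 30%, rho = 0.5: 0.2745/0.25 = 1.098, error about 5.8%

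**The case against.** The best defence has four parts.

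- **The analysis text is silent; it does not say participants are independent.** This is a condensed article, and variance estimators and covariates are commonly left to a full protocol or SAP that is not shown. That stands as far as the analysis goes. It does not reach the sample size, where the independence assumption follows from the number itself.
- **The size is unknown.** Expecting some people to come together does not mean they will be a large share, and Participant Recruitment relies partly on letters to individual patients. The article offers no evidence on how strongly outcomes agree within pairs. This stands: every figure for f and rho is an assumption, and in the 10%, 0.2 case the planned 80% power survives.
- **The pairs can be recovered.** The shared study number identifies them, so nothing is lost before analysis. This also stands, and it is why the remedy is cheap.
- **Leaving out therapist offsets the effect.** It does so in part. Under the assumed 40% and 60% strata, the first scenario becomes slightly conservative.

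A reader might infer that the true one-sided error certainly exceeds 5%, or that ignoring therapist is a second threat to validity. The documents support neither. The first depends on f, on rho and on how therapist is handled. The second has the wrong sign, because leaving out a balanced stratum widens the interval and cannot by itself produce a false claim of non-inferiority.

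**Conclusion.** The point holds in a limited, conditional form. The plan randomises people who attend together as a unit, sizes the trial as if all participants were independent, and describes a primary comparison that does not provide for the shared unit. The mismatch between allocation and sample size is firm. The effect on the analysis is conditional on the comparison being run as described and on positive correlation within pairs.

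Given both conditions, and setting aside the therapist offset, the error runs towards declaring non-inferiority. It is modest over plausible assumptions: from nothing noticeable when f × rho is about 0.02 or less, to about 6.3% one-sided error and 75.8% power at f = 30% and rho = 0.5. It does not undermine the design. It is worth correcting because it touches the primary inference and the data needed are already collected.

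**What to change.** 1. Estimate the primary risk difference, and the relative risk, with standard errors clustered on the study number without its A/B suffix. With pairs only, the number of clusters is 700 × (1 − f/2), for example 665 at f = 10% or 595 at f = 30%. That is ample for a robust variance.
2. Report by arm how many participants were co-allocated.
3. State under Power calculation that the 80% assumes independent participants.
4. Separately, for precision, include therapist (the stratification factor) in the primary model, and optionally baseline FTND, which the schedule of measures already collects. Standardise the result to the risk-difference scale so that it still answers to the 9.5-point margin.

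The cost is a sentence or two in the analysis section and one in the power section, with no new data and no change to conduct. The downside is that the interval may widen slightly if many pairs enrol.
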